**IgE-mediated FA proven by medical interview**

IgE-mediated FA is determined by study physicians’ interviews. IgE-mediated FA is considered positive if participants have a history of immediate adverse reactions to causal food within 2 hours after ingesting it during the study.

**Wheezing proven by medical interview**

Wheezing is defined if participants have a history of wheezing and determined by study physicians’ interviews during the study.

**Sensitization**

Sensitization is defined as a serum specific IgE titer of 0.35 UA/mL and over.

**Adherence index** An adherence index is determined by the percentage of TCSs applied in accordance with the protocol (days of actual TCS application/days of TCS application required in the study protocol). Good adherence is defined as an adherence index of 70% or more. Poor adherence is defined as an adherence index of less than 70%.

**Age in days and age in weeks** Birth day is defined as an age of 0 days. Age in weeks is defined as listed below.

| Age in weeks | | Age in days | | |  |
| --- | --- | --- | --- | --- | --- |
| 1 | week | 0 | – | 6 | days |
| 2 | weeks | 7 | – | 13 | days |
| 3 | weeks | 14 | – | 20 | days |
| 4 | weeks | 21 | – | 27 | days |
| 5 | weeks | 28 | – | 34 | days |
| 6 | weeks | 35 | – | 41 | days |
| 7 | weeks | 42 | – | 48 | days |
| 8 | weeks | 49 | – | 55 | days |
| 9 | weeks | 56 | – | 62 | days |
| 10 | weeks | 63 | – | 69 | days |
| 11 | weeks | 70 | – | 76 | days |
| 12 | weeks | 77 | – | 83 | days |
| 13 | weeks | 84 | – | 90 | days |
| 14 | weeks | 91 | – | 97 | days |
| 15 | weeks | 98 | – | 104 | days |
| 16 | weeks | 105 | – | 111 | days |
| 17 | weeks | 112 | – | 118 | days |
| 18 | weeks | 119 | – | 125 | days |
| 19 | weeks | 126 | – | 132 | days |
| 20 | weeks | 133 | – | 139 | days |
| 21 | weeks | 140 | – | 146 | days |
| 22 | weeks | 147 | – | 153 | days |
| 23 | weeks | 154 | – | 160 | days |
| 24 | weeks | 161 | – | 167 | days |
| 25 | weeks | 168 | – | 174 | days |
| 26 | weeks | 175 | – | 181 | days |
| 27 | weeks | 182 | – | 188 | days |
| 28 | weeks | 189 | – | 195 | days |

**Nutrition** Nutrition methods are defined as follows:

Breastfeeding: ingesting maternal breast milk

Regular cow’s milk formula feeding: ingesting regular cow’s milk formula

Hypoallergenic infant formula feeding: ingesting partially hydrolyzed and extensively hydrolyzed formulas

Mixed feeding: ingesting by both breastfeeding and infant formula feeding

Weaning food: ingesting semi-solid and/or solid foods

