5.6.3 Aggressive intervention group: Early aggressive treatments with topical corticosteroids

(Proactive method)

Basic whole-body treatment

Participants will be followed as described below and administered basic whole-body treatment, except for scalp.

Emollients

|  | Whole body except scalp |
| --- | --- |
| Registration day (Day 0) of the study  to 28 weeks of age | Hirudoid^®^ Soft ointment  every day  twice a day |

Topical corticosteroids

|  | Face | Body except scalp and face |
| --- | --- | --- |
| Registration day (Day 0) to Day 14 of the study | Almeta^®^ ointment  every day  twice a day | Rinderon^®^-V ointment  every day  twice a day |
| Day 15 of the study  to 28 weeks of age | Almeta^®^ ointment  two days per week  twice a day | Rinderon^®^-V ointment  two days per week  twice a day |

If participants do not have remission of atopic dermatitis on the 14th day (visit 2) after registration, daily administration of topical corticosteroid steroids is continued until day 28 (visit 3) after registration.

Additional skin rash treatment

Participants are to apply TCSs as additional treatment as described below:

| Face | Body except scalp and face | Scalp |
| --- | --- | --- |
| Day 15 of the study  to 28 weeks of age | Day 15 of the study  to 28 weeks of age | Day 15 of the study  to 28 weeks of age |
| Almeta^®^ ointment  every day until rash remission  , twice a day | Rinderon^®^-V ointment  every day until rash remission, twice a day | Rinderon^®^-V lotion  every day until rash remission  , twice a day |

Note:

When skin rash recurs, participants should re-apply TCSs on their body daily until they obtain remission of the skin rash.

If participants do not have remission from the skin rash by applying Rinderon^®^-V ointment for 7 days, they are permitted to use Fulumeta^®^ ointment.

When ointment is removed by washing or wiping, it can be re-applied.

Participants should frequently apply ointment to the area around the mouth to keep the skin around their lips covered with ointment.

5.6.4 Conventional treatment group: Standard treatment based on the Guidelines for the Management of Atopic Dermatitis (2016) (1) (Step-up reactive method)

Basic whole-body treatment

Participants will be followed as described below and administered basic whole-body treatment, except for scalp.

|  | Whole body except scalp |
| --- | --- |
| Registration day (Day 0) of the study  to 28 weeks of age | Hirudoid^®^ Soft ointment  Every day  twice a day |

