## 8.2 SECONDARY ENDPOINTS

EFFICACY ENDPOINTS

1. Food challenge test scores at the age of 28 weeks
2. Total IgE antibody titer in serum at the age of 28 weeks
3. Egg white, ovomucoid, milk, soy, wheat, and peanut-specific IgE antibody titers in serum at the age of 28 weeks
4. Egg white, ovomucoid, milk, soy, wheat, and peanut-specific IgG4 antibody titers in serum at the age of 28 weeks
5. Eczema Area and Severity Index (EASI) scores at 2, 4, and 8 weeks after study entry and at the age of 28 weeks
6. Patient Oriented Eczema Measure (POEM) scores weekly through the study
7. Percentage of disease-free days throughout the study
8. Dose of rescue medication used throughout the duration of the study
9. Infants’ Dermatitis Quality of Life Questionnaire (IDQoL) at 2, 4, and 8 weeks after study entry and at 28 weeks of age
10. Family Impact of Childhood Eczema Questionnaire (DFI) at 2, 4, and 8 weeks after study entry and at 28 weeks of age
11. Cumulative incidence of IgE-mediated FA assessed by a doctor’s interview during the study
12. Cumulative incidence of wheezing assessed by a doctor’s interview during the study

Justification for secondary endpoints (efficacy)

(1) Scoring of the food challenge test has already been recommended in the American Academy of Allergy, Asthma & Immunology – European Academy of Allergy and Clinical Immunology PRACTALL consensus report (65).

(2) (3) To evaluate allergy sensitization

(4) To evaluate immune tolerance against hen’s egg

(5) (6) To evaluate the activity and severity of AD

(7) (8) To evaluate the disease control

(9) (10) To evaluate the QoL

(11) To evaluate the prevalence of other IgE-mediated FA except hen’s egg

(12) To evaluate the prevalence of signs related to asthma

SECONDARY ENDPOINTS (SAFETY)

1. Serious adverse events
2. Adverse drug reactions
3. Salivary cortisol concentrations at 2, 4, and 8 weeks after study entry and at the age of 28 weeks
4. Body weight and body height at the age of 28 weeks

Justification for secondary endpoints (safety)

(1) (2) To evaluate safety of the study drugs

(3) To evaluate the effect on adrenal function by adverse drug reactions to TCSs

(4) To evaluate the effect of adverse drug reactions to TCSs on growth

ADHERENCE EVALUATION

(1) TCS adherence index in accordance with the protocol

(2) Dose of TCS used during the study

Justification for adherence evaluations

(1)(2) To evaluate adherence to the protocol

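### The steroid adherence index is an uncapped, unmatched ratio of day counts, so over-use is classed as good adherence and extra days can offset omitted ones

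*Protocol*

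**What the plan says.** Section 3 (Definitions, Adherence index) opens with a description: "An adherence index is determined by the percentage of TCSs applied in accordance with the protocol". It then gives the formula in brackets, "days of actual TCS application/days of TCS application required in the study protocol", and the cut-off: "Good adherence is defined as an adherence index of 70% or more". Anything lower is poor. There is no upper limit, no requirement that a counted day be a required day, and no rule for a zero denominator.

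Section 8.2 lists "TCS adherence index in accordance with the protocol" as the first of two adherence evaluations. The second is the dose of TCS used. The stated purpose of both is to evaluate adherence to the protocol.

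The required days come from section 5.6:
- **Aggressive arm (5.6.3):** TCS daily for "Registration day (Day 0) to Day 14 of the study", then "two days per week" until 28 weeks of age. If there is no remission at Day 14, "daily administration of topical corticosteroid steroids is continued until day 28 (visit 3) after registration". A recurrent rash also calls for daily use until remission.
- **Conventional arm (5.6.4):** TCS only while a qualifying rash is present. Less-mild rash on the face or body calls for none; scalp rash of any severity does.

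**The concern.** The arms differ largely in when steroid is called for. A conventional-arm infant who drifts towards the other regimen does so by using steroid on days that do not require it, which is over-use. An uncapped ratio of totals rewards over-use instead of flagging it. It also lets surplus days at one time pay for omitted days at another.

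The description and the formula pull apart. The description speaks of application in line with the protocol, but the formula counts any day of use. At stake is whether the good/poor label means what a reader will take it to mean, and whether it means the same in two arms where one denominator is largely fixed by schedule and the other is driven by rash.

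**Working it through.** The protocol gives no computed adherence figure, so there is none to reproduce. The check applies the printed formula to example infants.

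**Inputs**
- Formula and 70% cut: section 3.
- Aggressive arm: 15 daily days (Day 0 to Day 14), then 2 days in 7: section 5.6.3.
- Follow-up: 126 days, an assumed value. The age table in section 3 gives entry at 42–90 days and the endpoint at 189–195 days of age, so the last study day lies between 99 and 153.
- Conventional arm: 20 required days, an assumption for illustration.

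**Aggressive arm, 126 days, rash-free from Day 15**
- Required days: 15 + (126 − 15) × 2/7 = 15 + 31.7 = 46.7.
- TCS every day: 126/46.7 = 270%, good.
- First 15 days skipped, then 3 days a week: 111 × 3/7 = 47.6; 47.6/46.7 = 102%, good.
- First 15 days skipped, then 2 days a week as scheduled: 31.7/46.7 = 68%, poor. The offset in the previous line comes entirely from the extra days.

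**Range over permitted entry and end ages**
- Required days run from about 39 to 55, and daily use throughout scores 255% to 281%.
- With the extension to Day 28, required days are about 49 to 65, and daily use throughout scores 203% to 238%.
- Skipping the first phase and then using 3 days a week scores 93% to 109%, good at every entry age.
- Skipping it and then using 2 days a week scores 71% to 73% for entry at week 7 (good) and 62% to 65% for entry at week 13 (poor). The same omission is labelled differently by age at entry.

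**Conventional arm**
- 20 required, TCS on all 126 days: 126/20 = 630%, good.
- 20 required, 20 used, only 6 of them on required days: 20/20 = 100%, good, although 6/20 = 30% of required days were treated.
- 0 required, 0 used: 0/0, undefined.

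**If the numerator is read as concordant days only**
- The 270% and 630% cases both become 100%. They are still good, and the over-use is invisible.
- The 102% case falls to 31.7/46.7 = 68%, poor. This reading cures offsetting but not over-use.

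**The case against.** The strongest reply is that the opening description already limits the index to applications that follow the protocol, so the bracket is shorthand and ratios above 100% cannot arise. This is a fair reading of intent. The formula does not say it, however, and as shown above it would cap the ratio without detecting over-use.

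Several limits also stand:
- The 270% figure belongs to an infant with no rash after Day 15. Daily use during a recurrence, or up to Day 28 without remission, is itself required.
- The 102% case needs two departures that happen to cancel.
- An undefined index should be uncommon, since entry requires diagnosed atopic dermatitis with a recent itchy rash. It remains possible because there is no severity floor at entry. A zero-denominator rule alone could be left to the SAP.

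A reader might infer that the flaw corrupts the per-protocol analysis. The documents do not support that. Section 9.2 defines the per-protocol set by absence of significant deviation and does not mention the index, and sections 9.3.2 to 9.3.4 do not use it. A reader might also infer that the trial has no means of showing that the regimens differed. That goes too far. Section 8.2 also lists the dose of TCS used, section 6.1 collects amounts at visits and days of application daily, and sections 5.6.4 and 12.2.1 record a switch from the conventional to the aggressive regimen as a deviation.

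**Conclusion.** The point holds for the adherence evaluation and no further. Section 3 fixes both a formula and a cut-off, so this is not detail awaiting the SAP. By that formula, over-use is classed as good adherence (270% and 630% in the examples), and surplus days can conceal omission of the whole first phase (102%). The index is also undefined in the uncommon conventional-arm case with no required days. The figures rest on 126 days of follow-up, no rash after Day 15 in the aggressive-arm examples, and an assumed 20 required days in the conventional arm. The direction does not depend on the 126 days: daily use in a rash-free aggressive-arm infant exceeds 250% at every permitted entry age. The primary analysis is unaffected. The definition should be corrected because, as it stands, the label cannot distinguish following the assigned regimen from exceeding it.

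**What to change.** Replace the single ratio in section 3 with two components taken from the treatment diary:

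- **(a) Under-use:** required days on which TCS was applied, divided by required days. Section 5.6.3 does not name the two weekly days, so count that phase per week and cap it at the required number. Apply the 70% cut to this component.
- **(b) Over-use:** days on which TCS was applied when not required, divided by days not required. Report it separately by arm, and do not let it raise (a).
- State that a component with no eligible days is not applicable.

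On the 126-day examples:

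| Infant | Printed index | (a) | (b) |
| --- | --- | --- | --- |
| Aggressive, daily throughout | 270% | 100% | 79.3/79.3 = 100% |
| Aggressive, skip 15 days, then 3 a week | 102% | 31.7/46.7 = 68% | 15.9/79.3 = 20% |
| Conventional, 20 required, 126 used | 630% | 20/20 = 100% | 106/106 = 100% |
| Conventional, 20 required, none used | 0% | 0/20 = 0% | 0/106 = 0% |

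Here 79.3 = 126 − 46.7, 15.9 = 111 × 1/7 and 106 = 126 − 20.

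Do not apply the 70% cut to a single score of concordant days over all days. Rash-free days would mask complete non-treatment: the last infant in the table would score 106/126 = 84% and be called good.

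The cost is definition wording and some programming. The diary already records application and rash severity (section 5.6.1), so no new data are needed.

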# 4 ELIGIBILITY

Infants with AD who meet all of the following inclusion criteria and none of the exclusion criteria

## 4.1 INCLUSION CRITERIA

Infants (7–13 weeks old) who develop an itchy rash within the previous 28 days and receive a diagnosis of AD based on the U.K. Working Party’s diagnostic criteria

Justification for inclusion criteria

All infants with AD, including those with a family history of AD, will be included. The reason is that we would like to apply the study results for all infants with AD, not only for infants with a specific family background. As the U.K. Working Party’s diagnostic criteria is validated and has been widely used in various intervention studies internationally (66), we will apply the criteria in our study as well. Martin *et al.* reported that 20% of infants at 1 year of age who had a history of eczema received a diagnosis of FA (38). There were 50.8% of infants (95%CI: 42.8, 58.9) with early eczema onset (<3 months) who required doctor-prescribed topical corticosteroid treatment who developed challenge-proven FA. Shoda *et al.* demonstrated that in each age stratum (by month), infants with onset of eczema within the first 1–2 months after birth had the highest risk of FA at 3 years of age (aOR 6.61; 95%CI: 3.27, 13.34; *p*<0.001) (14). Infants who develop AD in early infancy are considered to have a higher risk for later FA and the defined target population in the PACI study is infants at the age of 7–13 weeks. We will exclude infants less than 6 weeks of age because differential diagnosis is difficult between AD and other skin diseases such as seborrheic dermatitis. Infants with AD at the age of 7 weeks and over are target populations because AD diagnosis is available.

## 4.2 EXCLUSION CRITERIA

1. Infants born before 37 weeks of gestation
2. Twin or multiple
3. History of emollient (heparinoid cream: Hirudoid^®^ Soft ointment) and TCSs (alclometasone dipropionate: Almeta^®^; betamethasone valerate: Rinderon^®^-V; mometasone furoate: Fulumeta^®^) side effects
4. History of taking oral or intravenous steroids within the previous 28 days
5. History of taking immunosuppressive agents (cyclosporine, tacrolimus, and so forth) or biologics, except vaccinations or intravenous immunoglobulins, within the previous 28 days
6. IgE-mediated hen’s egg allergy
7. Infants whose immediate family plans to move and who may not be able to visit the study site at 28 weeks of age
8. Parents unable to understand Japanese
9. Unwillingness to adhere to the study requirements and procedures
10. Infants with severe disease and other skin diseases that affect dermatological evaluation and study physicians judge that they are not appropriate for study participation

Justification for exclusion criteria

(1) The corrected age should be applied to infants with preterm birth.

(2) Siblings could potentially be treated with study drugs in error.

(3) Participants cannot apply the study drugs.

(4) (5) (6) (7) (8) These criteria affect the evaluation of the primary outcome.

(9) (10) The parents would not provide informed consent.

# 5 STUDY PROCEDURES

## 5.1 STUDY DESIGN

This study is a multicenter, investigator-blinded, randomized, parallel group controlled trial.

5.1.1 **Aggressive intervention group**: Early aggressive treatments with topical corticosteroids (proactive method)

Hanifin *et al.* performed an RCT for participants who were at least 3 months old and who had moderate or severe AD, to examine the efficacy of proactive therapy (21). Early aggressive treatments are modified from the Hanifin *et al.* study intervention, and details are described in section 5.6.1.

5.1.2 **Conventional treatment group**: Standard treatment based on the Guidelines for the Management of Atopic Dermatitis (2016) (1) (Step-up reactive method)

Standard treatment is based on the Guidelines for the Management of Atopic Dermatitis (2016) (1), and the details are described in section 5.6.1.

5.1.3 ANTICIPATED PARTICIPANTS AND STUDY DURATION

Anticipated number of participants: N=650 (aggressive intervention group: n=325 and conventional treatment group: n=325)

Duration of the study registration: 2 years from the day of IRB approval

Duration of the study intervention: 3 years after IRB approval

The study duration will be from study entry until completion of primary outcome assessment or until study termination. During the study duration, study treatment is continued unless the study treatment discontinuance criteria are satisfied. The study duration will be postponed under IRB approval if the study is not completed as scheduled.

Justification for the anticipated number of participants

Palmer *et al.* performed a double-blind, randomized controlled trial for infants with AD to test whether or not one-sixth of a raw whole egg taken every day can prevent development of IgE-mediated egg allergy. The infants were allocated to receive 1 teaspoon of pasteurized raw whole egg powder (n=49) or rice powder (n=37) daily from 4 to 8 months of age (67). A high proportion (31% [15/49]) of infants randomized to receive egg had an allergic reaction to the egg powder and 20% (10/49) had a reaction at the first ingestion of egg powder (one-sixth of a raw whole egg) at 4 months of age. When the control group participants received half of a raw egg provocation test at 12 months, 51% (18/35) were diagnosed with IgE-mediated egg allergy. These data suggested that prevalence of egg allergy in infancy is likely to depend on the provocation dose of egg and the preparation of egg such as heated or raw, and also on age and race of the participant. Therefore, we estimate that at least 30% of the participants in the conventional treatment group in this study will be diagnosed with IgE-mediated hen’s egg allergy using an oral food challenge test at the age of 28 weeks. However, the prevalence of IgE-mediated hen’s egg allergy among infants treated with early aggressive intervention for AD has never been reported. In Japan, it is common that infants at the age of 28 weeks do not eat hen’s eggs, and the prevalence of hen’s egg allergy at the age of 28 weeks in Japan is unclear. We consider a clinically effective prevalence of infants with early aggressive intervention for AD to be 20%. As discussed above, the calculated sample size is 614. Taking into consideration that the rate of drop out is about 5%, we determined the anticipated number to be 650.

EXPECTED PARTICIPANTS

In 2015, about 1,500 babies at the National Center for Child Heath and Development, 500 at Keio University Hospital, and 500 at Hamamatsu University Hospital were born. The total number of newborn babies was 2,500. According to a national survey in Japan, the prevalence of infants at the age of 6 months with AD or suspected history of AD was about 25% (10). From this previous result, we estimate that there will be about 625 newborn babies who are eligible participants. We assume that half of them (n=312) each year will visit one of the investigational sites for this Study because this is an intervention study. Therefore, we will recruit the expected participants in 2 years. In addition, we plan to increase the number of investigational sites.

## 5.2 REGISTRATION

This study uses VIEDOC^TM^ selected as the Electronic Data Capture system (EDC) by **Pharma Consulting Group Japan K.K.** to register and allocate participants.

Registration procedure

1. Prior to registration in this study, patients as candidates are listed on the patient list-up form (Supplement 1). Study physicians confirm eligibility criteria using the candidate confirmation sheet (Supplement 2). Based on the result of the confirmation of eligibility criteria, study physicians obtain informed consent for study participation using a fixed document request from the proxy (parent or legal guardian) of the participants who meet all of the inclusion criteria and none of the exclusion criteria. If a patient is determined to be ineligible, study physicians record the result on the patient list-up form (Supplement 1).
2. Study physicians input patient information to the EDC for the patient with informed consent. The information is checked immediately by the EDC and a participant identification number is issued and study treatment is assigned if eligibility is satisfied.
3. Participant identification number and assignment group are immediately displayed on the EDC and automatically notifies the principle investigator at the study site, study physician, research secretariat, and data center via e-mail. The principle investigator at the study site prints the assignment information and stores it in the case file.
4. The study physician confirms the assignment result and carries out the assigned study treatment.

Notes on registration

1. For participants who meet ineligibility and withdraw consent before registration, information is not entered into the electronic case report (eCRF).
2. When input of patient information is incomplete, registration can not be accepted until all items are input.
3. Eligibility is confirmed on the registration screen, and completion of registration is made as participant identification number is issued.
4. Registration is not cancelled for participants once they are registered.
5. When misregistration or duplicate registration is found, the data center must be promptly contacted using e-mail.
6. When duplicate registration is made, the prior registration is prioritized.

